#### Missing values

There are virtually no missing data from entry information in the CLARICOR trial [10, 12]. We expect missing laboratory data to be MCAR due to the fact that we know that some serum samples are missing either due to missing blood sample in the first place or due to a vial being damaged (see discussion). We will use Little’s test to decide whether a multiple imputation or a complete case analysis should be conducted [49]. Thus, each analysis of an advanced predictor will be initiated by Little’s test which will include all covariates with missing values (the standard biochemical predictors plus the advanced biochemical predictor to be assessed) plus all other variables in the model.

#### Supplementary exploration

Additional supplementary analyses include (1) an analysis of the impact of alternative GFR definitions and (2) an assessment of whether chance imbalance of new biochemical predictors may dramatically change the original findings of the CLARICOR trial.

The creatinine-based GFR will be used as our quantitative measure of kidney function in this study. Within the framework of the model that we will develop, we will in a separate report compare the predictive power of different formulas to estimate GFR (creatinine-based GFR, cystatin C-based GFR, or a combined creatinine/cystatin GFR formula). We will divide participants in GFR categories (GFR >60, 30–60, and <30 mL/min/1.73 m^2^) according to each specific GFR equation. We will then study the impact of reclassification across the GFR categories by the different GFR equations, by assessing the risk of adverse outcomes in those who were reclassified to a higher GFR category or to a lower GFR category, compared to those who were not reclassified.

Finally, we will assess if skewness (chance imbalance) in any predictors may explain the increased cardiovascular and all-cause mortality in participants who received clarithromycin as compared with placebo participants, i.e. we will repeat the analysis of the effect of clarithromycin but this time include the biochemical prognostic markers identified in the above described study.

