#### The patients

The patient group is defined by the inclusion and the exclusion criteria of the patients who, during the winter 1999–2000, entered the CLARICOR trial.

The CLARICOR trial was an investigator-initiated, randomised, placebo-controlled, multicentre superiority trial including outpatients with stable coronary artery disease (CAD), using central 1:1 randomisation and blinding of all parties. All patients discharged from wards or outpatient clinics in the Copenhagen area were available in an existing database. We invited all 13,702 patients who were alive and aged 18–85 years in 1999 and identified with a diagnosis of myocardial infarction or unstable angina pectoris during the years 1993–1999 to visit one of five cardiology centres in the Copenhagen area. Six thousand one hundred sixteen (44.6%) patients accepted the invitation, and of these, 4372 (71.5%) were randomised, while 1567 (25.6%) were excluded, and 177 (2.9%) refused to participate. Exclusion criteria included AMI or UAP within the previous 3 months, percutaneous transluminal coronary angioplasty and coronary bypass surgery within the previous 6 months, impaired renal or hepatic function, congestive heart failure (New York Heart Association (NYHA) IV classification of heart failure), active malignancy, incapacity to manage own affairs, breast feeding, and possible pregnancy. Between October 1999 and April 2000, the 4372 patients were randomised to receive oral clarithromycin 500 mg once daily for 2 weeks versus matching placebo to assess the effects on the risk of major cardiovascular outcomes and death.

The main results of the CLARICOR trial were that clarithromycin increased the risk of cardiovascular as well as all-cause mortality [12–14].

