##### Classification of the predictors

We have chosen collectively to classify as ‘standard predictors’ the below mentioned groups of predictors, i.e. (1) clinical predictors, (2) current medical treatment, and (3) standard biochemical predictors. The term ‘standard predictors’ is only a collective term used by us in this particular study to refer to those baseline quantities that were available to us during the CLARICOR trial and which are either established prognostic predictors or proxies of such predictors not available to us [31, 32]. The biochemical predictors we have measured in addition for the present PREMAC study are labelled ‘advanced biochemical predictors’. The two groups of predictors, i.e. ‘standard predictors’ and ‘advanced biochemical predictors’ are defined below.I.Standard predictorsClinical predictorsSex, age, smoking history, history of myocardial infarction compared to angina only, hypertension, and diabetes.Current medical treatmentAspirin (Yes/No), beta-blocker (Yes/No), calcium-antagonist (Yes/No), ACE-inhibitor (Yes/No), long lasting nitrate (Yes/No), diuretic (Yes/No), digoxin (Yes/No), statin (Yes/No), and anti-arrhythmic drugs (Yes/No). The current medical treatment was included as proxy predictors because information about post-infarction heart failure and post-infarction angina pectoris are not available to us.Standard biochemical predictorsHigh-sensitivity-reactive protein, glomerular filtration rate (GFR) estimated by creatinine, and lipoproteins (total cholesterol, HDL cholesterol, LDL cholesterol, triglycerides, apoprotein A1, and apoprotein B).
II.Advanced biochemical predictorsN-terminal pro-B-type natriuretic peptide, YKL-40, osteoprotegerin, hs-cTnT, PAPP-A, cathepsin B, cathepsin S, sTNFR1, sTNFR2, NGAL, endostatin, and calprotectin. Tests for all these quantities are commercially available.

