#### Flow of analyses

For each advanced biochemical quantity, we will examine if the hazard ratio of the biochemical quantity is different from 1.00 with a *P* value <0.01 when used alone and when used in combination with the standard predictors (forced to be included in the analyses whether they are significant or not). Using centre ID as a class variable, we will stratify on centre ID implying that the observations are conditionally independent within centres and that the coefficients of the covariates are the same across centres.

For each outcome, we will test for interaction between sex and each clinical predictor, each standard biochemical predictor, and each advanced biochemical predictor using Bonferroni adjusted *P* values and 0.05 as a threshold. The interactions corresponding to adjusted *P* values below 0.05 will be included in the model. Explanation will be sought for any marked discrepancies between the two settings (candidate used alone and candidate used in combination with standard predictors); but we will let us be guided by the results obtained when the latter setting is used.

Those advanced biochemical quantities which have a hazard ratio different from 1.00 and a *P* value <0.01 when used in combination with the standard predictors in the initial ‘gatekeeper’ analysis, will be included in subsequent and similar analyses of each individual outcome of the composite outcome.

We will use the *P* values of the analyses as a data-reducing device where a threshold of *P* < 0.01 is used at each decision node on our way to identify a candidate biochemical predictor among the advanced biochemical predictors. We regard the set of selected advanced biochemical predictors as the primary result of this essentially hypothesis-generating effort. However, clinically implausible results will be discussed and commented on.

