## Discussion

The present PREMAC study is important mainly for two reasons. First, new prognostic indicators are needed to improve preventive interventions in patients with ischaemic heart disease. Second, if known or new prognostic indicators show skewness between the two intervention groups at entry into the CLARICOR trial, this may help us better understand the harmful effects of clarithromycin. However, in previous publications we found no skewness of hs-CRP [15], N-terminal-pro-B-type natriuretic peptide [17], PAPP-A [18], YKL-40 [16], osteoprotegerin [25], and hs-cTnT [17].

The strengths of the CLARICOR trial are the considerable size of the patient population, long duration of follow-up, very few losses to follow-up (0.5%), the ethnic homogeneity of the patient population, and rarity of missing values. However, the values of 20 biochemical quantities have been added to the CLARICOR data and these data have missing values. The set of placebo patients with one or more missing biochemical quantity values includes 210 patients out of 2199 placebo treated patients giving 210/2199 = 9.5% patients having one or more biochemical quantity values missing. The percentage missing for the individual biochemical quantities ranges between 1.6 and 5.7%.

Potential weaknesses of the present cohort include the lack of information about left ventricle function, body mass index, blood pressure, and changes in medications during the follow-up period, and the fact that the prognosis of this type of patients today may have changed somewhat from the year 2000. Information about post-infarction heart failure and post-infarction angina pectoris was not available to us. Therefore, we added information about the medication at entry into CLARICOR as proxy information instead. The lack of information about left ventricular ejection fraction may be partially or completely compensated as Solomon et al. [32] found that age, sex, hypertension, prior AMI, creatinine, diuretics, digoxin, and mineralocorticoid receptor antagonist were related to left ventricular ejection fraction, all quantities that we have included within the group referred to as ‘standard predictors’.

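### The GFR reclassification analysis sets movers against one undivided non-reclassified group; the contrast is confounded by starting GFR and, if unadjusted, can make a correct upward move look harmful

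*SAP article*

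**What the plan says.** The SAP article, Supplementary exploration, compares three ways of estimating GFR: "creatinine-based GFR, cystatin C-based GFR, or a combined creatinine/cystatin GFR formula". It plans two things.

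- **Predictive power.** "Within the framework of the model that we will develop, we will in a separate report compare the predictive power of different formulas".
- **Reclassification.** "We will divide participants in GFR categories (GFR >60, 30–60, and <30" mL/min/1.73 m²), once per equation. Risk of adverse outcomes is then assessed "in those who were reclassified to a higher GFR category or to a lower GFR category, compared to those who were not reclassified".

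The second item gives the direction of the move and one reference group. It does not say which equation defines the starting category, whether the reference is limited to patients from that category, or whether the comparison is adjusted.

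Three other places bear on this. Classification of the predictors lists "glomerular filtration rate (GFR) estimated by creatinine" as a standard biochemical predictor. Flow of analyses has the standard predictors "forced to be included in the analyses whether they are significant or not". The patients section lists "impaired renal or hepatic function" as an exclusion, without a cut-off.

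**The concern.** The aim is to learn what a change of category under another GFR equation says about risk. That calls for comparing a patient who moved with one who began in the same category and stayed. The stated reference mixes non-movers from all three categories, so starting GFR differs between the groups by construction.

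The up-movers contain nobody who started above 60, while the reference contains everyone who started there and stayed. If that group is large and at low risk, up-movers can look worse than non-movers even when the new equation is right to move them up. The report could then mark down a better equation. The upward group also pools moves from below 30 with moves from 30–60, which start at different risk.

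**Working it through.** The plan gives no GFR distribution, risk by category or event count for this analysis, so there is no figure to reproduce. Step 1 follows from the text alone. Steps 2 to 4 use assumed inputs and show only direction and rough size.

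**Step 1. Who can be in each group**

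| Starting category | Can move up | Can stay | Can move down |
|---|---|---|---|
| >60 | no | yes | yes |
| 30–60 | yes | yes | yes |
| <30 | yes | yes | no |

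The movers and the reference therefore draw on different starting categories.

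**Step 2. Algebra for the 30–60 to >60 move**

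Let p1, p2, p3 be the shares of non-movers in >60, 30–60 and <30, and r1, r2, r3 their risks.

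- Reference risk: R = p1·r1 + p2·r2 + p3·r3.
- Up-mover risk: r1 + λ(r2 − r1). At λ = 0 up-movers carry the average >60 risk; at λ = 1, the average 30–60 risk.
- Up-movers look worse than the reference when λ exceeds (R − r1)/(r2 − r1).

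Assume risks 0.45, 0.65, 0.85 and shares 0.75, 0.23, 0.02. Then R = 0.3375 + 0.1495 + 0.0170 = 0.504, and break-even λ = 0.054/0.20 = 0.27.

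- λ = 0.5: risk 0.55. Risk ratio 0.55/0.504 = 1.09 against the undivided group, 0.55/0.65 = 0.85 against same-start non-movers.
- λ = 0: 0.45/0.504 = 0.89 against the undivided group, so no reversal.
- A fully correct move from <30 to 30–60: 0.65/0.504 = 1.29 undivided, 0.65/0.85 = 0.76 same start.

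With 90%, 75%, 60% or 40% of non-movers above 60, break-even λ is about 0.11, 0.27, 0.43 or 0.65. The reversal comes easily when >60 dominates and with difficulty when it does not.

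**Step 3. Simulation**

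Assumed: true GFR normal, SD 18, mean as shown; creatinine equation with error SD 12; new equation virtually error-free; hazard ratio 1.3 per 10 mL/min lower GFR; cumulative hazard 0.7 at GFR 75; 300,000 patients per setting. Hazard ratios against non-movers:

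| Mean GFR | Non-movers >60 | Up, undivided | Up, undivided + creatinine GFR | Up, same start | Down, undivided | Down, same start |
|---|---|---|---|---|---|---|
| 85 | 94% | 1.57 | 0.81 | 0.61 | 2.21 | 2.32 |
| 75 | 84% | 1.37 | 0.79 | 0.64 | 1.79 | 2.02 |
| 65 | 66% | 1.18 | 0.76 | 0.62 | 1.46 | 1.82 |
| 50 | 31% | 1.01 | 0.76 | 0.62 | 1.14 | 1.68 |
| 45 | 21% | 0.96 | 0.76 | 0.62 | 1.08 | 1.69 |

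With error SD 8 in the new equation, the undivided ratio for moving up was 1.67, 1.45, 1.26, 1.05 and 0.99 in the same order. Downward moves keep their direction but are diluted, most when >60 is a small share.

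**Step 4. Which adjustment**

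A second assumed setting had mean 75, SD 18, error SD 10 for both equations, hazard 2% lower per unit and cumulative hazard 0.7 at GFR 75. Risk was 60.7% in up-movers and 48.8% in all non-movers (60.7/48.8 = 1.24). Within the 30–60 start it was 59.0% against 67.1% (59.0/67.1 = 0.88). The hazard ratio for moving up against the undivided group was 1.39 unadjusted, 0.90 adjusted for creatinine GFR, and 1.18 adjusted for the new equation's GFR in its place.

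**The case against.** **The wording is silent rather than explicit.** The sentence does not say all, pooled or unadjusted; the article is condensed and defers the GFR work to a separate report. This stands in part. However, a comparator is stated, and on a plain reading it is one undivided group. That is a rule a later analyst would follow, not a detail left out.

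**The model may adjust for it.** Creatinine GFR is a forced standard predictor, and adjusting for it removed the reversal in every Step 3 setting. This is the strongest objection, and it is why the point must be conditional. It does not dispose of the point: the reference to the model's framework governs the predictive-power sentence and is not carried to the reclassification sentence. Comparing equations could also mean replacing creatinine GFR by the alternative, and in Step 4 that left the ratio above 1.

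**The GFR mix is unknown.** This stands. That >60 dominates is an inference from an exclusion with no cut-off.

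**The below-30 group.** A reader might infer from the renal exclusion that it is almost empty. The documents do not show that. An illustrative 1.4% would be about 31 of 2199 placebo patients (0.014 × 2199), which is sparse but not empty.

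**Little depends on it.** This also stands: the analysis is supplementary in a study that calls itself exploratory and hypothesis generating.

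**Conclusion.** The point holds in conditional form. The stated comparison is confounded by starting GFR; that follows from the category structure and needs no assumption. Whether the confounding reverses the apparent effect of a correct upward move depends on two things the plan does not settle: whether creatinine GFR is adjusted for, and how many patients are above 60. Under the assumed inputs of Step 3, the unadjusted hazard ratio for moving up was 1.18 to 1.67 when about two thirds or more of non-movers were above 60, and 0.96 to 1.05 when about a fifth to a third were.

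Two stronger readings are not supported. A reader might infer that the analysis gives the wrong sign; it can, but it need not. A reader might also infer that the study could then not tell which GFR equation predicts better; the plan compares predictive power separately, and that comparison is untouched. So is the selection of biomarkers, which the plan calls its primary result. The change is worth making because it is cheap and the uncorrected result could be misread.

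**What to change.** In Supplementary exploration, name creatinine-based GFR as the index equation. State that up-movers and down-movers will be compared, separately, with non-movers in the same creatinine-based starting category, using a Cox model stratified by that category or adjusted for creatinine GFR. If adjustment is chosen, say that creatinine GFR stays in the model and is not replaced by the alternative estimate. Pool <30 with 30–60 only if the <30 stratum proves too sparse, and report the number in each starting category.

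The cost is one or two sentences in the plan and one stratification variable or covariate in the analysis. No new data are needed.

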## Discussion

The present PREMAC study is important mainly for two reasons. First, new prognostic indicators are needed to improve preventive interventions in patients with ischaemic heart disease. Second, if known or new prognostic indicators show skewness between the two intervention groups at entry into the CLARICOR trial, this may help us better understand the harmful effects of clarithromycin. However, in previous publications we found no skewness of hs-CRP [15], N-terminal-pro-B-type natriuretic peptide [17], PAPP-A [18], YKL-40 [16], osteoprotegerin [25], and hs-cTnT [17].

The strengths of the CLARICOR trial are the considerable size of the patient population, long duration of follow-up, very few losses to follow-up (0.5%), the ethnic homogeneity of the patient population, and rarity of missing values. However, the values of 20 biochemical quantities have been added to the CLARICOR data and these data have missing values. The set of placebo patients with one or more missing biochemical quantity values includes 210 patients out of 2199 placebo treated patients giving 210/2199 = 9.5% patients having one or more biochemical quantity values missing. The percentage missing for the individual biochemical quantities ranges between 1.6 and 5.7%.

Potential weaknesses of the present cohort include the lack of information about left ventricle function, body mass index, blood pressure, and changes in medications during the follow-up period, and the fact that the prognosis of this type of patients today may have changed somewhat from the year 2000. Information about post-infarction heart failure and post-infarction angina pectoris was not available to us. Therefore, we added information about the medication at entry into CLARICOR as proxy information instead. The lack of information about left ventricular ejection fraction may be partially or completely compensated as Solomon et al. [32] found that age, sex, hypertension, prior AMI, creatinine, diuretics, digoxin, and mineralocorticoid receptor antagonist were related to left ventricular ejection fraction, all quantities that we have included within the group referred to as ‘standard predictors’.

Selection bias is also a potential weakness of the study. Only 2.6% of the patients selected for the CLARICOR trial refused to participate. So far that problem seems negligible. However, among those 7586 patients who declined our invitation to visit a cardiology centre, many must have been eligible for the CLARICOR trial, and we do not know how they looked and fared. So selection bias is a possibility.

The design of the CLARICOR trial may also contribute to selection bias. In the CLARICOR trial, the rate of cardiovascular events and deaths was studied in patients who had contracted an AMI or UAP during the period January 1993 to August 1999, were alive during the randomisation period (October 1999 to April 2000) and fulfilled the inclusion criteria and none of the exclusion criteria as defined in the CLARICOR trial [10].

Normally, to assess the rates in stable CAD patients, one would have started the study in January 1993 by including consecutively each patient who contracted an AMI or UAP, monitor the patient at regular intervals, say monthly from then on, note when the patient fulfilled the stability criteria (i.e. entered the stable state) and when the patient left the stable state again, and noting the characteristics of the new state (e.g. death). The patients included in such a design would differ from those of the CLARICOR trial in that they would include patients who entered the stable state and then died before October 1999. These patients are missing in the present PREMAC study. Thus, using the data to predict the prognosis of patients with stable CAD (as defined by the CLARICOR group), the results may very well be biased. This is the reason why we emphasise that the PREMAC study is an exploratory and hypothesis generating study.

We confined the net reclassification indices to the increase in the true-positive rate and the decrease in false-positives by including only two risk groups because when there are more than two risk categories, the indices do not adequately account for clinically important differences in shifts among risk categories [47]. We did not use category-free net classification indices because they suffer from many of the same problems as similar measures such as, e.g. the area under the receiver operating characteristic curve does. Besides, it can mislead investigators by overstating the incremental value of a biomarker, even in independent data [50].

A single number summary of the prediction increment would be the improvement in net benefit. This would require us to know the ratio between the cost of falsely classifying an event as a non-event and the cost of classifying a non-event as an event. (If this ratio was 3:1, it would dictate a predicted risk of 25% as a decision threshold; the cut at 25% mentioned above was foreseen to be an illustrative cut and was not suggested to be a clinical decision threshold.) We do not know which value of this ratio will be appropriate; anyhow, we may decide to adapt the Vickers-Elkin net benefit diagram [51] to the PREMAC context.

Clearly, the prognosis for the occurrence of all-cause mortality or CV mortality as predicted by the baseline values may very well change once it becomes known that one of the non-fatal vascular outcomes has occurred. Thus, this valuable outcome information should be studied not only in its role as being an outcome as described above but also in its role as being a predictor of all-cause mortality and CV mortality. We plan to analyse these time-series aspects in a subsequent study using intervening MI and UAP as predictive events.

